##### Consideration for machine learning modeling

The novel lung cancer recurrence prediction model will be constructed based on machine-learning algorithms (section 5.2). For the model development, we adopt a ratio of 6:2:2 for the training, validation, and test sets. This division ratio is based on the consideration that 60% training provides adequate data for model fitting and feature selection, while 20% validation allows unbiased hyperparameter tuning, and 20% test ensures a fully held-out assessment to guard against overfitting. This ratio balances model complexity and evaluation rigor, as recommended for medium-sized cohorts.^[21, 22, 23]^ When 173 patients are recruited for statistical power in the training set, a total of 289 cases are required.

In summary, to address the above three dimensions of statistical consideration and the disruption caused by loss to follow-up, we plan to enroll 300 patients in the first phase. This provides sufficient power for survival analysis while also accommodating downstream modeling requirements.

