### Machine learning model development and validation

The patients recruited in the first phase of this study will be randomly divided into training set, test set and validation set according to the ratio of 6: 2: 2. Considering the “events per variable” (EPV) rule, we apply the following steps to develop a robust recurrence prediction model. First, we will not treat all molecular features as separate predictors. Instead, we will compute summary metrics to reduce dimensionality (see section 5.1). Then Least Absolute Shrinkage and Selection Operator (LASSO) regression will be applied within the training subset to identify the most informative predictors, where the penalty parameter will be selected *via* grid search in nested 5-fold cross-validation. This procedure typically yields less than 9 variables, satisfying EPV≥10 given an expected 80 events (26.7% of the 300 patients).

All parameter tuning will be confined to the training set to avoid information leakage. Machine learning-based classifiers will be implemented on the training set with 1000 rounds of ten-fold cross validation. In each round, the training set will be split into 10 subsets (folds); in each fold, a model will be trained on nine of the subsets and then validated on the remaining subset to tune the hyperparameters. Then we will apply all obtained models to the test set and compare the performance measurements. The optimal method will be used to construct the final model. The tested algorithms included: adaptive boosting (AdaBoost), decision tree, logistic regression, linear support vector machine (Linear SVM), radial basis function kernel support vector machine (RBF SVM), naive Bayes, nearest neighbors, neural net, quadratic discriminant analysis (QDA), random forest, and extreme gradient boosting (XGBoost). All machine learning algorithms have a solid research foundation.^[35]^

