We will assess C statistics (area under the receiver-operator characteristic curve [ROC-AUC]), calibration, and clinical utility (decision-curve analysis) in the validation and test set. Finally, we determined an algorithm for developing predictive models, which has been widely popularized in the machine learning community and has excellent scalability, high running speed and state-of-the-art accuracy. It has better average performance than other algorithms in tests. Therefore, it is chosen for further optimization. The model willed be externally and respectively validated on two additional cohorts of NSCLC patients from published database^[10,11]^ and subsequent phases of the CLEVER study to confirm reproducibility and generalizability. If necessary, we will recruit a multi-center prospective multi-region cohort from collaborating institutions of medical alliance for further verification.

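### The algorithm is chosen on the test set that the plan calls held out, so the chosen model's test-set AUC is biased upward, by an amount the documents do not fix

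*Protocol article*

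**What the plan says.** All references are to the protocol article.

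- **Consideration for machine learning modeling** assigns the roles in the 6:2:2 split. Training is for fitting and feature selection, validation is for hyperparameter tuning, and "20% test ensures a fully held-out assessment to guard against overfitting". The section ends with the enrolment target: "we plan to enroll 300 patients in the first phase".
- **Machine learning model development and validation** repeats the split ("randomly divided into training set, test set and validation set according to the ratio of 6: 2: 2") but changes the roles. LASSO and all tuning stay inside the training set. Eleven algorithms are listed: AdaBoost, decision tree, logistic regression, linear SVM, RBF SVM, naive Bayes, nearest neighbors, neural net, QDA, random forest and XGBoost. After cross-validation in training, "Then we will apply all obtained models to the test set and compare the performance measurements", and "The optimal method will be used to construct the final model".
- **The same section** then plans to assess AUC, calibration and "clinical utility (decision-curve analysis) in the validation and test set". Of the selected algorithm it says: "It has better average performance than other algorithms in tests. Therefore, it is chosen for further optimization". External validation is planned in two published cohorts and in later CLEVER phases.

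**The concern.** Choosing one algorithm out of 11 is a fitting step. The plan's safeguard against leakage covers parameter tuning, not this choice. When the same 60 patients both pick the winner and supply its AUC, the reported value is the largest of 11 noisy estimates, and on average that exceeds the winner's true AUC. The property claimed for the test set in the sample-size section is then false as the plan is written.

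A recurrence prediction model is a stated aim of the study, and two of the three sample-size considerations are built around it. An optimistic internal AUC would become the benchmark for the later external and next-phase validations, and the choice of algorithm would itself be partly noise.

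The sections also disagree about the validation set. One gives it tuning. The other confines tuning to training and gives it no tuning or selection role. A reader cannot tell which internal set is reserved for the final assessment.

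**Working it through.** **1. The plan's own figures, reproduced.**
- Precision formula: 1.96² × 0.9 × 0.1 / (0.1² × 0.2) = 172.9, so 173.
- Training share: 173 / 0.6 = 288.3, so 289. This matches "When 173 patients are recruited for statistical power in the training set, a total of 289 cases are required".
- Enrolled: 300. Training 0.6 × 300 = 180; test 0.2 × 300 = 60; validation 60.
- Events among 60 test patients: 0.20 × 60 = 12 (rate in the recurrence-prediction calculation), or 80/300 × 60 = 16 (rate in the modelling section).

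**2. Noise in one test-set AUC.** Hanley–McNeil, with Q1 = A/(2−A), Q2 = 2A²/(1+A), n₁ events and n₀ non-events:

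SE² = [A(1−A) + (n₁−1)(Q1−A²) + (n₀−1)(Q2−A²)] / (n₁n₀).

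Example, A = 0.80, n₁ = 16, n₀ = 44: [0.16 + 15 × 0.0267 + 43 × 0.0711] / 704 = 3.618/704 = 0.00514, so SE = 0.072.

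**3. Rough size of the selection effect.** For 11 equally good algorithms with correlation ρ, the expected excess of the best is about 1.586 × SE × √(1−ρ), where 1.586 is the expected maximum of 11 standard normals. At A = 0.80, 16 events and ρ = 0.5: 1.586 × 0.072 × 0.707 ≈ 0.08. Simulation of the same setting gives 0.073. The approximation ignores the ceiling at 1, so the simulated values are used below.

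**4. Simulation.** Correlated binormal scores, 60 patients, 11 algorithms with equal true AUC, winner chosen by test AUC, ρ from 0.3 to 0.9. *Assumed, not in the documents:* the true AUC, ρ, equality of the algorithms, and selection on AUC itself.

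| True AUC | SE, 12 / 16 events | Mean inflation, from ρ = 0.3 with 12 events to ρ = 0.9 with 16 events |
|---|---|---|
| 0.70 | 0.091 / 0.081 | 0.110 to 0.042 |
| 0.80 | 0.081 / 0.072 | 0.091 to 0.036 |
| 0.90 | 0.062 / 0.054 | 0.059 to 0.025 |
| 0.965 | 0.038 / 0.033 | 0.028 to 0.014 |

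The last two rows represent the plan's anticipated accuracy. Sensitivity and specificity of 0.90 correspond to an AUC of 0.90 for a single cut-off, or Φ(2 × Φ⁻¹(0.9)/√2) = 0.965 under a binormal model. At 0.965 the inflation cannot exceed 1 − 0.965 = 0.035.

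**5. Unequal algorithms.** With true AUCs spread ±0.05 around 0.75, mean inflation is 0.089 to 0.023. With ±0.10 it is 0.064 to 0.013.

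**6. Fitted classifiers.** Eleven classifiers of the listed types (gradient boosting in place of XGBoost) were fitted on 180 patients, with selection on 60 and true AUC measured in new cases. Mean inflation was 0.086, 0.065 and 0.040 at 20% events, and 0.073, 0.059 and 0.041 at 26.7%. The chosen model's true AUC ran from about 0.59 to 0.80 (60 replicates per scenario, Monte Carlo standard error about 0.01).

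**7. After the fix.** Choosing on one set of 60 and scoring only the winner on a separate 60 gives mean inflation within ±0.003 of zero in every equal-AUC setting examined.

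**The case against.** The strongest reply is that the plan does not rest on the test set alone. Under the modelling section as written, the validation set takes no part in tuning or selection, yet performance is also reported there, so those 60 patients would give an estimate that the choice does not bias. Two published cohorts and later CLEVER phases follow. This stands, with limits. The sample-size section gives that same validation set to tuning, and the plan does not say which data the optimization after selection will use, so it is clean only if kept out of both. The Introduction describes the two published cohorts as limited by small size.

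A second reply is that the wording on average performance in tests may mean cross-validation, and that speed and scalability are also cited. The preceding paragraph nevertheless names the test set as the place of comparison. If cross-validation was meant, the text still needs correcting.

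Three stronger readings are tempting, and the documents do not support them:
- *That the AUC is inflated by a fixed 0.04 to 0.10.* This needs true AUCs of roughly 0.6 to 0.8, similar algorithms and selection on AUC. The plan speaks only of performance measurements and anticipates much higher accuracy, where the effect is smaller.
- *That all reported performance is overstated.* Only the test-set estimate is affected by the choice.
- *That calibration and net benefit are overstated too.* Only AUC was examined, and choosing on AUC need not improve apparent calibration.

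**Conclusion.** The plan is wrong as written on this point. The set described as held out is used to choose among 11 algorithms and then to report the winner's performance. The test-set AUC of the chosen model is biased upward, and the roles of the validation and test sets conflict between the sample-size and modelling sections.

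The direction was upward in every scenario examined; the size is an assumption. With 60 test patients and 12 to 16 events, mean inflation is about 0.04 to 0.11 for true AUC of about 0.6 to 0.8 with similar algorithms, and about 0.01 to 0.06 at the anticipated 90% sensitivity and specificity. Over all assumptions tried it is about 0.01 to 0.11.

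The validation-set estimate (if that set stays out of tuning, selection and later optimization), the external cohorts and the later phases are not biased by the choice. The primary endpoints, two-year DFS and OS, are not touched.

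**What to change.** Rewrite the two sections so that each set has one role:

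1. Choose the algorithm by cross-validated performance within the training set, or on the validation set. If by cross-validation, repeat the LASSO step inside each fold; otherwise the held-out folds have already informed feature selection.
2. Finish any further optimization without using the test set.
3. Lock the algorithm, hyperparameters and cut-off, then score that one model once on the test set. Show test results for the other ten algorithms as descriptive only.
4. State whether the validation set is for tuning, for selection or for assessment, and use the same wording in both sections.
5. If the test set has already been used to choose the algorithm, relabel it as a selection set. Take the internal performance estimate from the validation set if it is untouched, and otherwise from next-phase patients.

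The cost is wording, a reordering of analysis steps and a somewhat lower reported AUC. No new patients or data are needed, unless both internal sets have already been used, in which case the estimate waits for the next phase.

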##### Consideration for recurrence prediction validation

In this study, we aim to validate a machine-learning-based lung cancer recurrence prediction model with anticipated sensitivity of 90% ± 10% and specificity of 90% ± 10%. To calculate the necessary sample size for this diagnostic validation, we anchor our calculations to a fixed two-year recurrence (event) rate of 20%, based on retrospective study of recurrence after complete resection of early NSCLC.^[17, 18]^

Using Buderer’s formula for sensitivity and specificity sample size estimation:^[19, 20]^

$$N=\frac{Z^{2}\cdot p(1-p)}{d^{2}\cdot \text{ Prevalence }}=\frac{(1.96{)}^{2}\cdot 0.9\cdot 0.1}{0.1^{2}\cdot 0.2}\approx 173\text{ patients }$$

Here p is the anticipated sensitivity or specificity (0.90), d is the half-width of the 95% confidence interval (0.1), and Prevalence is the event prevalence (0.25). This calculation yields approximately 173 patients required to estimate sensitivity and specificity with ±10% precision at α = 0.05.

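### The recurrence model is sized on sensitivity and specificity, but the stated assessment names neither and fixes no cut-off at which to estimate them

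*Protocol article*

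**What the plan says.** Under *Consideration for recurrence prediction validation*, the protocol article sets the aim: "we aim to validate a machine-learning-based lung cancer recurrence prediction model with anticipated sensitivity of 90% ± 10% and specificity of 90% ± 10"%. The precision term is defined as follows: "d is the half-width of the 95% confidence interval (0.1"). The result is stated plainly: "This calculation yields approximately 173 patients required to estimate sensitivity and specificity with ±10% precision at α = 0.05".

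*Consideration for machine learning modeling* assigns the 173 patients to the 60% training share, obtains 289 in total, and rounds up to 300 to allow for loss to follow-up. The survival consideration states a need of only 172. As the plan counts, it is therefore the sensitivity and specificity target that carries the first-phase size.

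*Machine learning model development and validation* describes what will be done with the model. Candidate algorithms are compared on measures that are not named: "Then we will apply all obtained models to the test set and compare the performance measurements". The best one becomes the final model. Performance is then described: "We will assess C statistics (area under the receiver-operator characteristic curve [ROC-AUC]), calibration, and clinical utility (decision-curve analysis) in the validation and test set". External validation in published cohorts and later phases follows, again without a named measure. Neither that section nor *Statistical analysis* mentions sensitivity, specificity or a risk cut-off.

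**The concern.** Sensitivity and specificity belong to a classification rule. For a model that outputs a score, they have a value only once a cut-off is chosen. The plan spends its sample size on estimating them and then lists three other measures. AUC averages over all cut-offs, calibration concerns the predicted risks themselves, and a decision curve shows net benefit over a range of thresholds. None of these is an estimate of sensitivity and specificity at a stated operating point.

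This is more than a missing detail. Two parts of the same document say different things about how the model will be validated: one gives the target and sizes for it, the other gives the list of measures and leaves the target out. A reader of the results could be shown a respectable AUC as fulfilment of the validation aim and have no figure to set beside the anticipated 90%/90%.

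**Working it through.** **1. Reproduce the plan's figures.** Inputs, all from *Consideration for recurrence prediction validation*: p = 0.90, d = 0.10, Z = 1.96, and "a fixed two-year recurrence (event) rate of 20"%.

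- N = Z² p(1−p) / (d² × prevalence) = 1.96² × 0.9 × 0.1 / (0.1² × 0.20) = 172.9, rounded up to 173.
- 173 / 0.6 = 288.3, rounded up to 289. The planned 300 adds 11.

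Both figures reproduce. The text below the formula gives a different value ("Prevalence is the event prevalence (0.25"). With 0.25 the formula gives 138.3, or 139, so 173 rests on 0.20.

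**2. Which measure drives the size.** For specificity the denominator uses 1 − prevalence: 1.96² × 0.09 / (0.01 × 0.80) = 43.2, or 44 patients. Sensitivity therefore sets the number, and the formula amounts to 1.96² × 0.09 / 0.01 = 34.6, about 35 patients with recurrence.

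**3. What an AUC says about 90%/90%.** The documents give no score distribution, so this step is an assumption: equal-variance binormal scores with separation δ, for which AUC = Φ(δ/√2) and the point of equal sensitivity and specificity is Φ(δ/2).

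- For 90%/90%: δ = 2 × 1.2816 = 2.563, so AUC = Φ(2.563/√2) = 0.965.
- In the other direction:

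| AUC | Sensitivity = specificity | Sensitivity at 90% specificity |
|---|---|---|
| 0.75 | 68% | 37% |
| 0.80 | 72% | 46% |
| 0.85 | 77% | 57% |
| 0.90 | 82% | 70% |

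A check on the dependence on shape: any ROC curve through the 90%/90% point has an area of at least 0.9 × 0.9 = 0.81, because sensitivity is at least 0.9 wherever the false-positive rate exceeds 0.1. If the curve is also concave, the area is at least 0.1 × 0.9/2 + 0.9 × (0.9 + 1)/2 = 0.045 + 0.855 = 0.90. An AUC of 0.80 is thus incompatible with 90%/90% under any shape, and 0.85 under any concave shape.

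**4. Precision available in the held-out data.** The 6:2:2 split of 300 gives held-out sets of 60 and 60. The half-width for sensitivity is 1.96 × √(0.09/events), with event rates of 20%, 25% and 26.7% (the last from the 80 events expected in 300):

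| Held-out data | Events | Half-width for sensitivity |
|---|---|---|
| One set of 60 | 12 / 15 / 16 | ±17.0 / ±15.2 / ±14.7 points |
| Both sets, 120 | 24 / 30 / 32 | ±12.0 / ±10.7 / ±10.4 points |

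Exact intervals are wide: 11 of 12 detected gives 62% to 99.8%, and 14 of 16 gives 62% to 98%. Specificity in one set of 60 has a half-width of about ±8.5 to ±8.9 points, which is within target. The ±10 for sensitivity would need about 35 events in the evaluation data, and the 173 patients expected to supply them are placed in the training set.

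**The case against.** The strongest reply has four parts.

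- **The aim is estimation.** The 90% values are anticipated and the ±10% is a confidence interval half-width. There is no hypothesis and no pass mark. This stands. A reader might infer that a 90%/90% claim goes untested, or that success could be declared against a set criterion on a much weaker model. The document sets no such criterion, so the point is limited to a quantity that was sized for and then not listed.
- **A cut-off need not come from the evaluation data.** A reader might infer that, with no cut-off stated, one would have to be picked on the test set, with the optimism that brings. The plan confines parameter tuning to the training set, and a threshold is naturally read as such a parameter. The stronger reading is therefore not supported.
- **The outputs contain the quantities.** A ROC curve consists of sensitivity and specificity pairs, net benefit is built from true and false positives, some listed classifiers can return class labels directly, and the unnamed performance measurements might include both. This stands in part: the figures could be extracted, but nothing fixes the point at which to read them.
- **A journal article leaves detail to a full protocol or SAP.** That covers a list left out. Here a list is given, and it does not match the measures behind the sample size.

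The AUC equivalents rest on an assumed ROC shape. This also stands, and they serve only as illustration.

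**Conclusion.** The mismatch is real. The quantity that produced 173, 289 and 300 is absent from the stated performance measures, and no operating point is fixed. Under the binormal assumption, an AUC of 0.80 to 0.90 would leave both measures at about 72% to 82%, against an anticipated 90% that needs about 0.965. Other ROC shapes change these figures. The mismatch itself depends on no assumption.

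Adding the two measures would not by itself deliver the stated precision. For sensitivity the held-out data give about ±15 to ±17 points in one set and ±10 to ±12 with both pooled, assuming 90% true sensitivity, event rates of 20% to 26.7% and no losses. That is too imprecise to support a pass/fail rule in a set of 60. The primary endpoints, DFS and OS, are not affected.

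**What to change.** In *Machine learning model development and validation*:

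1. Add sensitivity and specificity for two-year recurrence at one cut-off fixed in the training set, in line with the plan's own rule on tuning. Report them with exact 95% confidence intervals in the held-out data, and keep AUC, calibration and decision curves beside them.
2. Name one training-set measure, such as cross-validated AUC, for choosing the algorithm, in place of an unnamed comparison on the test set.

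In *Consideration for recurrence prediction validation*, replace the ±10% by the precision the held-out data give, state the prevalence once, and set no pass/fail requirement.

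Alternatively, if AUC is the intended target, replace the calculation there by a precision calculation for AUC.

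The cost is wording in these sections and a few lines of output, best settled before outcome data are analysed. The downside is that a fixed cut-off and the restated precision may look less favourable than a tuned cut-off and ±10%.

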### Statistical analysis

The Wilcoxon test is used to compare distribution differences in genomic and transcriptomic biomarkers between groups, while Fisher’s exact test is applied to compare clinical variables and the number of gene mutations between groups. All p-values are two-sided, with *P* < 0.05 considered statistically significant.

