### Sample collection

#### Tissue samples

In order to accurately sample and record the position, we have developed a standardized multi-region sampling process. Initially, the surgical sample is dissected along its maximum diameter. Equal-sized samples are then taken from one side of the tumor using a skin perforator. For smaller tumors, consider sampling from various locations on the opposite side. Samples from at least two tumor regions must be separated by 0.3 cm to 1 cm, depending on the tumor size, for inclusion in the study. Border samples should be collected at the interface between tumor and normal tissue to ensure that both tumor and normal samples are obtained. Paired normal tissue samples should be taken at least 2 cm away from the tumor edge. Last but not least, the central coordinates of each sampling point were recorded using a double-scale square and documented with photographs.

All tissue samples must be immediately placed into freezing tubes for preservation at -80°C. If the tumor is sufficiently large, a set of paraffin-embedded samples should also be collected for all tissues.

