### Whole exome sequencing and analysis

The DNA library is prepared with an input of 200 ng genomic DNA using the VAHTS Universal Plus DNA Library Prep Kit for Illumina V2. The subsequent hybridization capture is performed using the SureSelect XT target enrichment system. The final DNA library is quantified using the Qubit 3.0 and fragment detection is conducted with the Agilent 2100. Finally, the DNA library is sequenced using paired-end 150 bp reads on the Illumina NovaSeq 6000 platform.

The sequencing data is analyzed using the WES pipeline. The sequencing data from white cells is used to exclude germline mutations. Clean reads in FASTQ format are aligned to the human UCSC reference genome (hg19/GRCh37) using the Burrows-Wheeler Aligner (BWA, v0.7.15). Sambamba (v0.6.8) is used to process PCR duplicates in the mapped BAM files. The Genome Analysis Toolkit (GATK v4.0.11.0) is employed for local realignment and base quality recalibration to compute sequencing coverage and depth. Single nucleotide variations (SNVs) and small insertions and deletions (Indels: < 50 bp) are identified using GATK MuTect2 (v1.1.4). Multiple testing correction for gene-level mutation frequency comparisons will be performed using the Benjamini-Hochberg procedure, with an adjusted p-value (FDR) cutoff of < 0.05.

Based on multi-region sequencing, region-based tumor mutation calling is combined to recall tumor-informed mutations, allowing for the acquisition of new recalled mutations for each region. Using these recalled region-level mutations, the phylogenetic tree is reconstructed using the CNIPHER method,^[24]^ enabling the identification of clonal and subclonal mutations. Somatic copy number alterations (SCNAs) are processed using ASCAT (V2.3), which allows for the determination of intratumoral heterogeneity in both SNVs and SCNAs, specifically assessing subclonal mutation fractions and subclonal SCNAs fractions. This comprehensive analysis facilitates a deep understanding of evolutionary events within the tumor, characterized by intratumoral heterogeneity, clonal illusion, subclonal expansion, whole genome doubling, weighted genome integrity index (wGII), and loss of heterozygosity (LOH). These insights provide a detailed depiction of the tumor’s evolutionary landscape and its underlying genetic dynamics.

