### RNA sequencing and analysis

To construct a transcriptome sequencing library, 1–3 μg of total RNA is prepared using the VAHTS Universal V6 RNA-Seq Library Prep Kit for Illumina (NR604-01/02). The final RNA library is quantified using the Qubit 3.0, and fragment analysis is conducted with the Agilent 2100. Additionally, the Bio-RAD CFX 96 fluorescence quantitative PCR is used to quantify the effective concentration of the RNA library (ensuring it is greater than 10 nmol/L) using the Bio-RAD KIT iQ SYBR Green. The RNA library is then sequenced using paired-end 150 bp reads on the Illumina NovaSeq 6000 platform.

The sequencing data is aligned to the human UCSC reference genome (hg19/GRCh37) using the STAR aligner (version 2.7.4a) and annotated with ANNOVAR software. Subsequent analyses include immune cell infiltration assessment, identification of differentially expressed genes (DEGs), enrichment analysis, and subtypes clustering. DEGs will be identified with DESeq2, applying the Benjamini–Hochberg FDR correction. Genes with FDR < 0.05 and |log₂FoldChange| > 1 will be considered significant. These analyses aim to explore the heterogeneous tumor microenvironment, providing insights into the complex interactions and variations within the tumor.

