### GeoMx digital spatial profiling

A whole transcriptome atlas comprising 18,000 genes and a proteome atlas consisting of 570 proteins were generated using the GeoMx Digital Spatial Profiler (NanoString) on formalin-fixed, paraffin-embedded (FFPE) tissue sections. The slides were stained with morphological markers, including PanCK (epithelial cell marker), CD3 (lymphocyte marker), CD68 (macrophage marker), and DAPI (DNA marker). Based on these markers, 178 circular and polygonal regions of interest (ROIs), along with two negative controls, were selected for analysis.

Digital counts for each gene were standardized following quality control procedures. Protein digital counts were normalized using internal spike-in controls (ERCC) and the signal-to-noise ratio (SNR). DESeq-based differential expression analyses for both transcript and protein counts will include FDR control *via* the Benjamini–Hochberg method, reporting only targets with adjusted p-values < 0.05 as significant.

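### The blanket P<0.05 rule conflicts with the FDR rule for gene-level mutations and leaves other biomarkers without multiplicity control; the unit of analysis for multi-region and ROI data is not fixed

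*Protocol article*

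**What the plan says.** All references are to the protocol article.

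- *Statistical analysis* names two tests. For biomarkers: "The Wilcoxon test is used to compare distribution differences in genomic and transcriptomic biomarkers between groups". For the rest: "Fisher’s exact test is applied to compare clinical variables and the number of gene mutations between groups". It then sets one threshold: "All p-values are two-sided, with *P* < 0.05 considered statistically significant". It names no adjustment, and it states neither the Wilcoxon variant (rank-sum or signed-rank) nor the unit (patient, region or ROI).
- *Whole exome sequencing and analysis*: "Multiple testing correction for gene-level mutation frequency comparisons will be performed using the Benjamini-Hochberg procedure", with an adjusted cutoff of 0.05.
- *RNA sequencing and analysis*: "DEGs will be identified with DESeq2, applying the Benjamini–Hochberg FDR correction", with FDR below 0.05 and an absolute log2 fold change above 1.
- *GeoMx digital spatial profiling*: 178 ROIs are selected, and "DESeq-based differential expression analyses for both transcript and protein counts will include FDR control". Only targets with an adjusted p below 0.05 are reported as significant. The number of patients behind the ROIs and the model terms are not given.
- *Tissue samples*: "Samples from at least two tumor regions must be separated by 0.3 cm to 1 cm". Border tissue and paired normal tissue are also taken.
- *Study design and highlights* makes the search for predictors of clinical benefit the secondary endpoint.

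**The concern.** There are two separate problems.

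**Threshold.** The general section covers genomic and transcriptomic biomarkers and gene mutations by name, and it puts all of them at an unadjusted 0.05. For gene-level mutation comparisons the exome section requires FDR control. The same result could be called significant under one section and not under the other. Measures outside the three FDR families fall under the raw rule alone: subclonal mutation and copy-number fractions, wGII, LOH and immune infiltration scores. Finding predictors is the secondary endpoint, so this rule decides which markers the study will claim.

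**Unit of analysis.** Multi-region sampling defines this study, and regions of one tumour are correlated. A rank-sum test, or a DESeq model without a patient term, treats its rows as independent. If regions or ROIs are the rows and the groups differ between patients (for example, recurrence or not), the p values are too small. Benjamini-Hochberg applied afterwards does not repair p values that are already too small.

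**Working it through.** The plan gives no figure of its own here beyond alpha = 0.05, so there is nothing to reproduce. The number of biomarkers, the regions per patient beyond the minimum of two, the intraclass correlation (ICC) and the number of patients behind the 178 ROIs are not stated. They are assumptions below.

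**1. Which rule covers which comparison**

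| Comparison | Specific section | Statistical analysis section | Result |
|---|---|---|---|
| Gene-level mutation frequency | BH, adjusted p < 0.05 | Fisher, raw P < 0.05 | Conflict, if Fisher's test on gene mutations is this comparison (the natural reading) |
| RNA-seq differential expression | DESeq2, BH, FDR < 0.05 plus fold change | Wilcoxon for transcriptomic biomarkers, raw P < 0.05 | Boundary not drawn |
| GeoMx transcripts and proteins | DESeq-based, BH, adjusted p < 0.05 | Not named | Specific rule governs |
| Heterogeneity fractions, wGII, LOH, immune infiltration | No significance rule | Wilcoxon, raw P < 0.05 | No multiplicity control |

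**2. Cost of raw 0.05 over k null biomarkers**

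P(at least one false positive) = 1 − 0.95^k for independent tests; expected number = 0.05 × k.

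| k | P(at least one) | Expected number |
|---|---|---|
| 5 | 0.226 | 0.25 |
| 10 | 0.401 | 0.5 |
| 20 | 0.642 | 1.0 |
| 50 | 0.923 | 2.5 |
| 100 | 0.994 | 5.0 |

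In 2,000 simulated global-null runs, Benjamini-Hochberg at 0.05 brought P(any false positive) to about 0.05 for both 20 and 100 biomarkers, against 0.65 and 0.99 at raw 0.05.

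**3. Regions entered as separate observations in a between-patient contrast**

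Design effect DE = 1 + (m − 1) × ICC for m regions per patient; actual type I error = 2[1 − Φ(1.96/√DE)]. Example: m = 3, ICC 0.5 gives DE = 2.0, 1.96/1.414 = 1.386, error 0.166.

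The formula was checked by simulating the rank-sum test on pooled regions, 4,000 runs per cell. The groups were 80 versus 220 patients, taken from the article's expected 80 events among 300.

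| m | ICC | Formula | Simulation |
|---|---|---|---|
| 2 | 0.3 | 0.086 | 0.078 |
| 2 | 0.5 | 0.110 | 0.104 |
| 2 | 0.7 | 0.133 | 0.138 |
| 3 | 0.3 | 0.121 | 0.117 |
| 3 | 0.5 | 0.166 | 0.156 |
| 3 | 0.7 | 0.206 | 0.196 |

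With one mean per patient, the simulated error was 0.043 to 0.057 over all scenarios run (2 to 5 regions, ICC 0.1 to 0.9).

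**4. ROIs entered as separate observations in a between-patient contrast**

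The same formula, as an approximation to the DESeq-type test:

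- 178 ROIs from 10 patients: m = 17.8. At ICC 0.1, DE = 1 + 16.8 × 0.1 = 2.68 and the error is 0.231.
- 178 ROIs from 60 patients: m ≈ 3.0. At ICC 0.1, the error is 0.073.
- At ICC 0.3, the two cases give 0.425 and 0.120.

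**5. Within-patient contrast, pairing ignored**

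Take a shared patient effect, with m tumour regions and one normal sample per patient. The true variance of the difference is (1 − ICC)(1/m + 1), and an unpaired test assumes 1/m + 1. The ratio is 1 − ICC for any m, so the unpaired test is conservative. Simulation with one tumour and one normal sample from 300 patients gave type I error 0.022, 0.006 and 0.001 at ICC 0.3, 0.5 and 0.7.

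**The case against.** The strongest reply is that much of this is silence in a condensed article. No section says that regions enter as separate observations. The Wilcoxon test has a paired form, some heterogeneity measures are one value per tumour by construction, and a DESeq-type model accepts a patient term. Specific rules ordinarily override a general convention, and the matter concerns biomarker work rather than the DFS and OS primary endpoints.

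Part of this stands. A reader might infer three stronger claims that the article does not support:

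- **That multi-region data are tested as independent samples.** The article leaves the unit open. The inflation in steps 3 and 4 is conditional on pooling.
- **That raw 0.05 over the 18,000-gene panel yields 18,000 × 0.05 = 900 false positives.** That panel is the GeoMx atlas, which has its own Benjamini-Hochberg rule.
- **That tumour, border and normal markers will be declared too often.** Step 5 shows the opposite for tumour versus normal when pairing is ignored.

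The reply does not remove the threshold problem. The section states a rule for all p values and names these biomarkers, and several of them have no specific rule to override it. On the unit, the article names a test for ROI counts and gives finer details elsewhere (a matching caliper of 0.2, k = 15 for cell neighbourhoods). It mentions summary metrics only for the prediction model, not for the group comparisons.

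**Conclusion.** The concern holds in two parts of different strength.

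**Threshold: stated in the text.** The direct conflict is confined to gene-level mutation comparisons, and it rests on reading the Fisher test on gene mutations as that comparison. For biomarkers outside the three FDR families it is a gap: the chance of at least one false positive is 0.64 with 20 null biomarkers and 0.99 with 100. Those probabilities assume independence. Correlated biomarkers would generally give less, but the expected counts of 1 and 5 hold under any dependence.

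**Unit of analysis: not fixed.** If regions are pooled in a between-patient contrast, the error is about 9–13% at the stated minimum of two regions and 12–21% at three, for an assumed ICC of 0.3–0.7. For ROIs it is about 7–23% even at an assumed ICC of 0.1, if 10 to 60 patients contribute. For tumour versus normal within a patient, the cost of ignoring pairing is power.

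**What to change.** 1. In *Statistical analysis*, list the biomarker families and apply Benjamini-Hochberg at 0.05 within each, including heterogeneity measures, wGII, LOH and immune infiltration. Limit raw P<0.05 to single pre-specified clinical comparisons. State that Fisher's test on gene mutations follows the exome section's FDR rule, and where Wilcoxon rather than DESeq2 is used for expression.
2. State that the patient is the unit of analysis. For between-patient contrasts, use one summary per patient (or pseudobulk counts), or a patient random intercept.
3. For within-patient tissue and ROI contrasts, use the paired Wilcoxon form or a model blocked on patient, for example patient as a term in the DESeq2 design. State how many patients supply the 178 ROIs.

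The cost is a few sentences and slightly more modelling; no new data are needed. Fewer markers will be nominally significant, although pairing should gain power for tumour-versus-normal contrasts.
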